### Sample size {14}

The primary endpoint of this study is the number of unmet needs. Recent literature points out that PwDs have on average 1.87 unmet needs with a standard deviation of 2.0 [47]. The sample size calculation was based on an assumed reduction of the number of unmet needs of 35% and a randomization ratio of 1:2 (1: intervention group, 2: waiting list). In a previous study, where dementia care management was also carried out, and patients were recruited from GP practices, there was an intra-cluster correlation (ICC) of 0.16 with a variance of ICC of 0.06 and a cluster size of five (five patients per GP practice). This ICC, variance of ICC, and cluster size were also used to calculate the sample size for this study. Therefore, a sample size of *n* = 345 PwD and 69 clusters would be needed to demonstrate an implicit effect of 1.22 unmet needs in the intervention group compared to 1.87 unmet needs in the control group at a significance level of *α* = 0.05 and statistical power of 80%. A loss to follow-up of about 30% was assumed due to the elderly population and the inclusion of a waiting-list group. Overall, this requires the recruitment of *n*=465 participants of 93 clusters to demonstrate a significant intervention effect. Therefore, a total of *n* = 310 patients in the waiting-control group (recruited from 62 GP practices) and *n* = 155 patients in the intervention group (from 31 GP practices) will be necessary to detect a significant difference between the intervention and the waiting control group concerning a 35% reduction of unmet care needs.

The randomization ratio of 1:2 was used due to the higher probability of dropouts in the waiting control group, which is predominantly a problem in times of the COVID-19 pandemic and the introduced lockdowns, contact restriction and the high risk of severe COVID-19 progressions, subsequent hospitalization, and death in the elderly population.

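### The 0.06 given as the variance of the ICC is either mislabelled or leaves the planning ICC too imprecise to use, and at the stated ICC of 0.16 the stated 345 patients give about 60% power, not 80%

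*Protocol article*

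**What the plan says.** In the protocol article, section Sample size {14}, the planning values for clustering come from an earlier study of dementia care management in GP practices, where "there was an intra-cluster correlation (ICC) of 0.16 with a variance of ICC of 0.06 and a cluster size of five". The next sentence makes all three figures inputs to this trial: "This ICC, variance of ICC, and cluster size were also used to calculate the sample size for this study".

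The other inputs stand in the same section. The outcome assumption is that "PwDs have on average 1.87 unmet needs with a standard deviation of 2.0". The target is "an implicit effect of 1.22 unmet needs in the intervention group compared to 1.87 unmet needs in the control group", with 1:2 allocation, a significance level of 0.05 and "statistical power of 80" per cent. The resulting size before loss to follow-up is 345 patients in 69 clusters.

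The section does not give the number of practices behind the ICC, the estimator or the scale of the ICC, or how a variance of the ICC entered the calculation.

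**The concern.** A variance of 0.06 has a square root of 0.245, which exceeds the ICC of 0.16 that it is meant to qualify. An ICC that uncertain would be compatible with no clustering and with very strong clustering, and could not support a single power figure. If 0.06 is some other quantity, the label is wrong, and anyone who reworks the power or borrows the figure for a later trial starts from a false statement of its precision.

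The article also says that the ICC and its variance were used, so the stated size ought to reflect them. Whether it does decides whether the stated 80% can stand.

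**Working it through.** **Inputs** (all from Sample size {14}): ICC ρ = 0.16; variance of ICC 0.06; cluster size m = 5; means 1.87 and 1.22, so a difference of 0.65; SD 2.0; allocation 1:2; α = 0.05; power 80%; 345 patients in 69 clusters. Two-sided testing is an assumption, because the article does not state sidedness.

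**1. Reproducing the stated size.** With no allowance for clustering, the intervention arm needs

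n = (1.960 + 0.842)² × 2.0² × (1 + 1/2) / 0.65² = 7.849 × 4 × 1.5 / 0.4225 = 111.5, so 112.

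The control arm needs 222.9, so 223. The total is 335. In whole practices of five at 1:2 this is 23 + 46 = 69 practices, or 345 patients, exactly the stated figure.

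With the stated ICC the design effect is 1 + (5 − 1) × 0.16 = 1.64, and 335 × 1.64 = 549. So 345 is what results when neither the ICC nor the 0.06 is used. The alternatives tried with ICC 0.16 do not give 345 either: 433 one-sided, 489 at 1:1, and 197 to 230 with Poisson variances.

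**2. What a variance of 0.06 implies.** The large-sample variance of the analysis-of-variance ICC from k practices of equal size m is

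Var = 2(1 − ρ)²(1 + (m − 1)ρ)² / [m(m − 1)(k − 1)].

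With ρ = 0.16 and m = 5 this is 2 × 0.84² × 1.64² / [20(k − 1)] = 0.190/(k − 1).

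| Reading of 0.06 | Standard error | Implied practices k | 95% interval for the ICC |
|---|---|---|---|
| Sampling variance | 0.245 | 1 + 0.190/0.06 = 4.2 (about 21 patients) | −0.32 to 0.64 |
| Standard error (variance 0.0036) | 0.06 | 1 + 0.190/0.0036 = about 54 (about 270 patients) | 0.04 to 0.28 |

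Checks on the first row: a second variance formula needs 5 practices. Simulated overdispersed counts (mean 1.87, SD 2, ICC 0.16, five per practice) give a variance of 0.054 at 3 practices, 0.042 at 4 and 0.004 at 54. Smaller clusters raise the implied number to 7.8 practices at m = 3 and 16.8 at m = 2, which is still few.

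**3. Reading 0.06 as a variance component.** On the count scale with SD 2.0, a between-practice variance of 0.06 gives an ICC of 0.06/4 = 0.015; an ICC of 0.16 would need 0.16 × 4 = 0.64. As a log-scale random-intercept variance in a Poisson model with mean μ, the count-scale ICC is μ(e^0.06 − 1)/[1 + μ(e^0.06 − 1)]. This is about 0.10 at μ = 1.87 and 0.16 at μ near 3.1. The mean in the earlier study is not given, so this reading cannot be excluded.

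**4. Power at 345 patients in 69 practices** (115 against 230). SE = 2.0 × √[(1/115 + 1/230)(1 + 4ρ)], and power = Φ(0.65/SE − 1.96).

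| ICC | Design effect | SE | Power |
|---|---|---|---|
| 0 | 1.00 | 0.228 | 81% |
| 0.04 | 1.16 | 0.246 | 75% |
| 0.16 (stated) | 1.64 | 0.293 | 60% |
| 0.28 | 2.12 | 0.333 | 50% |
| 0.64 | 3.56 | 0.431 | 33% |

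**The case against.** The strongest objection is that the diagnosis leans on a study the reader cannot see. The four practices are not a document figure; they are solved from a formula that assumes equal clusters of five and an analysis-of-variance ICC, applied where a large-sample formula is least reliable. The lower limit of −0.32 even falls below the smallest ICC possible with clusters of five, −1/(5 − 1) = −0.25. This stands as a limit on precision: the number of practices is an inference, and the range in the variance case has to be truncated at zero. It does not rescue the label, because the second formula and the simulation give 3 to 5 practices.

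A reader might infer that 0.06 is simply a standard error. That reading would suit a practice-based trial, but the documents do not establish it. The primary analysis is a multilevel Poisson model, a random-intercept variance is another quantity that could have been reported, and on the log scale it can agree with an ICC of 0.16. In that case 0.06 says nothing about the precision of the ICC, and neither sensitivity range follows from it.

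A reader might also infer that the 0.06 caused the shortfall in power. It did not. The fall from 81% to 60% comes from leaving out the design effect, and relabelling alone would change neither 345 nor the stated 80%. Nor is planning on one ICC value an error in itself; it is common practice. What remains wrong is that the article claims to have used these inputs and states a power that they do not give.

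**Conclusion.** The point holds in a limited form. As labelled, 0.06 implies an ICC estimated from about 4 practices with a standard error of 0.245. So either the label or value is wrong, or the ICC is too imprecise to plan on. The documents do not say which, and they do not show that the earlier study was in fact that small.

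Separately from the label, the stated 80% is not the power of the stated design at the protocol's own ICC. With 345 patients analysed in 69 practices of five, it is about 60%. This rests on a difference of 0.65, a common SD of 2.0, equal clusters, 1:2 allocation, a normal approximation and a two-sided 5% test. The 50% to 75% and 33% to 81% ranges are conditional on what 0.06 turns out to be and are not findings in themselves.

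**What to change.** Trace the 0.06 to the earlier study. State whether it is a sampling variance, a standard error or a variance component, correct the label or the value, and give the number of practices behind the ICC.

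Restate power at 345 patients in 69 practices with the stated ICC: about 60% at 0.16, with the assumptions listed. Add a sensitivity range, marked as conditional:

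- if 0.06 is a standard error, about 75% down to 50% for an ICC of 0.04 to 0.28;
- if it is a true variance, about 81% down to 33% for an ICC of 0 (truncated) to 0.64, with a statement that the planning ICC is not reliable;
- if it is a variance component, neither range applies, and the precision of the ICC has to come from the earlier study.

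Correct the sentence that says these inputs were used, unless a calculation can be shown that uses them and gives 345. The cost is one traced figure and a short restatement. No patients are added and the planned analysis does not change; the downside is a less favourable stated power.

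### The 345 patients in 69 practices said to give 80% power do not follow from the printed inputs unless a decisive variance assumption was made that is not stated

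*Protocol article*

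**What the plan says.** The protocol article's section Sample size {14} sets out the inputs and the result together. On the outcome it says that "PwDs have on average 1.87 unmet needs with a standard deviation of 2.0", and it assumes a 35% reduction, that is 1.87 against 1.22. Allocation is one intervention patient to two waiting-list patients. An earlier dementia care management study supplies an ICC of 0.16 (with a variance of the ICC of 0.06) and five patients per practice, and the text adds: "This ICC, variance of ICC, and cluster size were also used to calculate the sample size for this study".

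It then concludes that "345 PwD and 69 clusters would be needed to demonstrate an implicit effect of 1.22 unmet needs in the intervention group", with alpha 0.05 and 80% power. An allowance of about 30% for loss to follow-up takes this to 465 patients in 93 practices (155 intervention, 310 waiting list). The abstract repeats 465 as the number needed. Neither place states whether alpha is one- or two-sided, the formula, or an SD for the intervention arm.

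**The concern.** Five patients per practice and an ICC of 0.16 inflate the required size by 64%. A figure that carries this inflation should be well above the individually randomised size. With the one SD that is printed, 345 is almost exactly the individually randomised size.

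If the power is really nearer 60 to 65% than 80%, a true 35% reduction would be missed in roughly one trial in three, and a null result could be read as evidence against an effect the trial was not sized to detect. This matters because the Discussion expects the results to inform the legal framework for such care models.

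**Working it through.** **Inputs, all from Sample size {14}:** means 1.87 and 1.22 (difference 0.65; exactly 35% would be 0.6545), SD 2.0, allocation 1:2, alpha 0.05, power 80%, ICC 0.16, five per practice. **Assumptions added here:** two-sided alpha, and a normal approximation for a difference in means.

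**Formula.** With control SD 2.0 and intervention-arm SD s, the intervention-arm size is n = (1.960 + 0.842)² × (s² + 2.0²/2) / difference² × DE. The squared sum is 7.849. The total is 3n. Whole practices are n/5 rounded up, times three.

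**Design effect.** DE = 1 + (5 − 1) × 0.16 = 1.64.

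**Reproducing the stated 345**

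| Calculation | Difference | Intervention n | Practices | Patients |
|---|---|---|---|---|
| Common SD 2.0, no design effect | 0.65 | 7.849 × 6 / 0.4225 = 111.5 | 23 + 46 = 69 | 345 |
| Common SD 2.0, no design effect | 0.6545 | 109.9 | 22 + 44 = 66 | 330 |
| Intervention SD in proportion to the mean, DE 1.64 | 0.65 | 7.849 × (1.70 + 2) / 0.4225 × 1.64 = 112.8 | 23 + 46 = 69 | 345 |
| Same | 0.6545 | 110.9 | 23 + 46 = 69 | 345 |

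In the last two rows the intervention SD is 2.0 × 1.22/1.87 = 1.30. A further route to 69 practices keeps the design effect and combines one-sided alpha with a variance proportional to the mean (332 patients before rounding to practices). The article states none of these assumptions.

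**The printed inputs taken at face value (SD 2.0 in both arms, DE 1.64).** n = 111.5 × 1.64 = 182.8, so the total is 548, or 37 + 74 = 111 practices and 555 patients. With 0.6545 the total is 541, again 111 practices.

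**Power at 345 (115 and 230).** SE = 2.0 × √1.64 × √(1/115 + 1/230) = 0.2925. Power = Φ(0.65/0.2925 − 1.960) = 60%. The difference detectable at 80% power is 2.802 × 0.2925 = 0.82 needs, a 44% reduction. A t-based version gives 59%.

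**Power at 465 recruited with 30% loss.** This leaves 108.5 and 217 patients, 3.5 per practice if losses are even, and DE = 1 + 2.5 × 0.16 = 1.40. SE = 0.2782 and power is 65%. The detectable difference is 0.78 needs, a 42% reduction. With no loss at all (155 and 310, DE 1.64) power is 73%.

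**Sensitivity to the unstated intervention-arm variance (two-sided)**

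| Intervention-arm assumption | Power at 345 | Power at 465 with 30% loss |
|---|---|---|
| SD 2.0, as in control | 60% | 65% |
| Variance proportional to the mean (SD 1.62) | 72% | 76% |
| SD proportional to the mean (SD 1.30) | 81% | 84% |

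**Other single changes, keeping SD 2.0 in both arms.** One-sided alpha needs 432 patients (72% power at 345). An ICC of 0.06 in place of 0.16 needs 415 (72%). An ICC of 0.22, if the stated variance of the ICC was meant as an upward allowance, needs 629 (55%).

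**The case against.** A reader might infer that the ICC was simply forgotten, because dropping it returns 69 practices and 345 patients. The article does not support that as a fact. It says plainly that the ICC and cluster size were used. The match without clustering also holds only for the rounded difference 0.65 and fails at 0.6545, whereas the calculation with the design effect and an intervention SD of about 1.30 gives 69 practices at both.

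A common SD of 2.0 is itself an added assumption. The 2.0 is quoted for people with a mean of 1.87, and no SD is given for a group with a mean of 1.22. For a count it is not the natural choice: the variance-to-mean ratio would rise from 4/1.87 = 2.1 to 4/1.22 = 3.3, while the planned Poisson model has variance falling with the mean. So 60% is the low end of the range for the variance assumptions tabulated, not an established property of the trial.

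Both arguments stand, and they limit what can be said about the cause and the size of the shortfall. They do not rescue the paragraph. A condensed article may leave the formula and software to a fuller document, but this one prints inputs and presents the result as following from them. Only an assumption that changes the answer from 555 patients to 345 makes that true. Nor can covariate adjustment be assumed to fill the gap. The section claims no gain from it, the statistical methods section makes adjustment conditional on observed baseline differences, and a baseline correlation of about √(1 − 345/548) = 0.61 would be needed.

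**Conclusion.** The stated size does not follow from the printed inputs. With SD 2.0 in both arms and two-sided alpha, the requirement is about 548 evaluable patients, not 345. Power is then about 60% at 345 and about 65% at the planned 465 with 30% loss.

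That the design effect was left out is one possible explanation and is not proven. Nor do the documents show that the trial is underpowered: an intervention SD of about 1.30 would bring power to about 81% and 84%. What holds is that the 80% claim rests either on an omission or on an unstated assumption that decides the answer, and the article does not show which. The figures rest on the normal approximation, even losses across practices and an ICC of 0.16.

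**What to change.** Rerun the calculation with ICC 0.16 and five patients per practice. Correct Sample size {14} and, if the figure changes, the abstract.

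- **If a common SD of 2.0 was used:** state that the planned 465 gives about 65% power for a 35% reduction after 30% loss, or 80% power for about a 42% reduction.
- **If a smaller intervention-arm SD was used:** state it with its justification, and give power across the plausible variance assumptions (60% to 81% at 345; 65% to 84% at 465 with 30% loss).

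In either case state the sidedness of alpha and how the variance of the ICC entered. Neither 548 nor 65% should be printed without the common-SD condition attached.

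Re-estimate the SD and ICC from data pooled over the arms, without using allocation, and report the updated power. Pooled data will not separate the two arms' SDs, so the range should stay.

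The cost is a change of wording, a short recalculation and possibly a less favourable stated power. No extra patients are required.

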**Methods:**

InDePendent is a two-arm, multi-center, cluster-randomized controlled intervention study. Inclusion criteria are age ≥70 years, cognitively impaired (DemTect ≤8) or formally diagnosed with dementia, and living in the own home. Patients will be recruited by general practitioners or specialists. Randomization is carried out at the physicians’ level in a ratio of 1:2 (intervention vs. waiting-control group). After study inclusion, all participants will receive a baseline assessment and a follow-up assessment after 6 months. Patients of the intervention group will receive advanced dementia care management for 6 months, carried out by specialized nurses, who will conduct certain tasks, usually carried out by primary care physicians. This includes a standardized assessment of the patients’ unmet needs, the generation and implementation of an individualized care plan to address the patients’ needs in close coordination with the GP. PwD in the waiting-control group will receive routine care for 6 months and subsequently become part of the intervention group. The primary outcome is the number of unmet needs after 6 months measured by the Camberwell Assessment of Need for the Elderly (CANE). The primary analysis after 6 months is carried out using multilevel models and will be based on the intention-to-treat principle. Secondary outcomes are quality of life, caregiver burden, acceptance, and cost-effectiveness. In total, *n*=465 participants are needed to assess significant differences in the number of unmet needs between the intervention and control groups.

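### The 345 evaluable patients, the loss of about 30% and the 465 recruits do not reconcile: 465 covers only about 26% loss

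*Protocol article*

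**What the plan says.** All the figures stand in one paragraph of the protocol article, Sample size {14}.

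- Evaluable requirement, for 80% power at a significance level of 0.05: "345 PwD and 69 clusters would be needed".
- Loss: "A loss to follow-up of about 30% was assumed due to the elderly population and the inclusion of a waiting-list group".
- Recruitment target, presented as what follows from these two: "465 participants of 93 clusters to demonstrate a significant intervention effect".
- By arm: "310 patients in the waiting-control group (recruited from 62 GP practices") and "155 patients in the intervention group (from 31 GP practices").

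The abstract (Methods) repeats the total: "465 participants are needed to assess significant differences in the number of unmet needs between the intervention and control groups". It gives no loss rate and no evaluable number. The document states no other loss rate and no other rule for inflating the sample.

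**The concern.** The paragraph prints a base, a loss rate and a result, and the result does not follow from the other two. This is not detail that an article leaves to a longer document, because all three numbers are printed.

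The practical cost is that a reader cannot tell what loss was planned for. Dropout is a central design issue here: the same section cites an elderly population, the waiting list and COVID-19, and gives higher expected dropout in the control arm as the reason for 1:2 allocation. When the trial reports its attrition, it should be possible to say whether it exceeded the plan. With 26% implied and about 30% stated, it is not. The number of evaluable patients at the stated loss also falls short of the number that the section says is needed.

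**Working it through.** **Inputs** (Sample size {14}): 345 evaluable patients in 69 practices; loss about 30%; 465 recruits in 93 practices (155 + 310 patients, 31 + 62 practices); five patients per practice; ICC 0.16; allocation 1:2; power 80%; alpha 0.05. Sidedness is not stated, so two-sided is assumed below.

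**Step 1. Try to reproduce 465.** At 1:2, 69 practices are 23 + 46, and 345 patients are 115 + 230.

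- Standard inflation: 345/(1 − 0.30) = 492.9, so 493.
- Same by practice: 69/0.70 = 98.6, so 99 practices (33 + 66), or 495 patients.
- Multiplier shortcut: 345 × 1.3 = 448.5, so 449; by practice 69 × 1.3 = 89.7, so 90 practices, or 450 patients.
- 30% loss in the control arm only: 115 + 230/0.70 = 444, or 115 + 230 × 1.3 = 414.

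None gives 465 patients or 93 practices. A multiplier of 1.35 does come out close (345 × 1.35 = 465.75; 23 × 1.35 = 31.05; 46 × 1.35 = 62.1). But the section uses 35% only for the assumed reduction in unmet needs, never as a loss.

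**Step 2. Solve back from 465.**

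- Loss that 465 covers: 1 − 345/465 = 25.8%.
- Evaluable at 30% loss: 465 × 0.70 = 325.5, about 326.
- Shortfall against 345: 345 − 325.5 = 19.5, or 5.7%.

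**Step 3. What this does to power.** Grant that 345 patients in 69 practices give exactly 80%. Power at another effective sample size is then Φ(2.8016 × √ratio − 1.96), where 2.8016 = 1.960 + 0.8416 and the ratio is the new effective size over the planned one. Effective size is N/[1 + (m − 1) × ICC], with m patients per practice. The loss is taken as equal in both arms.

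*Whole practices lost.* About 65 practices of five remain (93 × 0.70 = 65.1). The design effect is unchanged, so the ratio is 325.5/345 = 0.943 and power = Φ(0.761) = 77.7%.

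*Losses scattered within practices.* All 93 practices remain, with 5 × 0.70 = 3.5 patients on average.

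- Planned: 345/(1 + 4 × 0.16) = 345/1.64 = 210.4.
- After loss: 325.5/(1 + 2.5 × 0.16) = 325.5/1.40 = 232.5.
- Ratio 1.105; power = Φ(0.985) = 83.8%.

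*The same with uneven practice sizes.* If each patient is lost independently, the squared coefficient of variation of cluster size is (5 × 0.7 × 0.3)/3.5² = 0.086. The design effect becomes 1 + (1.086 × 3.5 − 1) × 0.16 = 1.448. The effective size is 325.5/1.448 = 224.8, and power is about 82.5%.

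*Sensitivity to a lower ICC.* The section gives 0.06 as the variance of the ICC. Used here purely as an alternative ICC, it gives 345/1.24 = 278.2 planned and 325.5/1.15 = 283.0 after scattered loss, with power 80.7%. With uneven sizes the effective size is 325.5/1.168 = 278.7, and power is about 80%.

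**The case against.** **The loss is given as 'about' 30%.** That allows some looseness, and 25.8% may simply have been rounded generously. But it reaches 30% only by rounding to the nearest ten. Even a loss of 27.5% would need 345/0.725 = 476 recruits. If roughly 26% was used, the text should say so. What stands is that this is imprecision in a stated rate, not proof of a faulty design.

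**The head count is the wrong measure in a clustered trial.** This objection is strong and largely stands. The reasons for loss that the protocol names are those of individual patients: age, hospitalisation and death under Sample size {14}; nursing-home admission, death and withdrawn consent under the discontinuation criteria {11b}. Nothing mentions practices dropping out. Under scattered loss, 326 patients in 93 practices carry at least as much information as 345 in 69.

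A reader might therefore infer that the mismatch leaves the trial underpowered at about 78%. The documents do not support that as a general result. The figure holds only if whole practices are lost or the ICC is zero.

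**493 or 495 looks like the corrected target.** A reader might infer this too, but the documents do not support it. Those numbers inherit whatever basis 345 has. From the stated difference of 0.65 and SD of 2.0, a two-sided 1:2 comparison of means needs about 335 patients without clustering and about 549 with a design effect of 1.64. A plain Poisson variance with the same design effect needs about 197. How 345 was derived is a separate question and is not settled here.

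**Conclusion.** The inconsistency is certain and rests only on printed numbers: 345 evaluable, about 30% loss and 465 recruits cannot be connected by any of the usual rules. The recruitment figure covers about 26% loss and leaves about 326 patients at 30%, some 20 (6%) below the stated requirement.

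The consequence for power is modest at most. On the plan's own premise that 345 patients in 69 practices give 80%, power is about 78% if entire practices are lost. It stays at or above about 80% if patients are lost within practices (about 82 to 84% at the stated ICC of 0.16). These figures assume a two-sided test and equal loss in both arms. They are conditional on the 80% premise, which this check does not test.

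The abstract is not wrong in itself: it states only 465, so it needs a change only if that number changes. The point is worth correcting because 465 is the headline number and the correction is cheap.

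**What to change.** Keep 465 and restate the loss in Sample size {14}, in one of two ways:

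1. Say that 465 recruits in 93 practices allow for about 26% loss while keeping 345 evaluable; or
2. Keep 30%, say that about 326 evaluable patients are then expected from 93 practices, and give the power recomputed with the ICC and the reduced average cluster size of about 3.5, stating whether loss is assumed within practices or of whole practices.

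If a different inflation rule was used, name it. If 493 (495 in whole practices) is mentioned at all, label it as the head-count inflation of 345 for 30% loss, not as a new target. Leave the abstract as it is unless 465 changes.

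The cost is a sentence or two of wording and, for the second option, one short calculation. Recruitment, allocation and analysis are untouched. The stated allowance for loss, or the stated evaluable number, becomes slightly less favourable.
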